#### Power analysis

We performed a series of power analyses using G*Power [44] and for each analytic method. Assuming a small effect size of 0. 2, we will be able to reject the null hypothesis with probability (power) of 1.00 (survival analysis, *N* = 750), 0.81 (logistic regression, *N* = 750), 0.88 (paird t-tests; *N* = 250) and 0.99 (linear regression, *N* = 250). The Type I error probability associated with these tests is 0.05. A detailed report is presented in Additional file 1.

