### Participant recruitment, eligibility and group assignment

Participants are recruited from Fairfield and Pickaway County Children Services. The overall case flow is provided in Fig. 1. Within 7 days of the initial child welfare investigation, parents complete the UNCOPE assessment, a universal screening tool for substance use administered to all parents entering the child welfare system [33]. Parents who score a 3 or higher on the UNCOPE, are considered eligible for EPIC and receive a drug screen. Eligible parents are alternated into EPIC, OhioSTART or treatment as usual (TAU). Ultimately, assignment to EPIC is determined based on caseload, but is typically offered to every third case in Fairfield county and every other case in Pickaway county. Parents who consent to EPIC are connected to peer recovery supporters who mentor parents through the process. Parents are also referred to FTDC with the option to receive MOUD, and lastly when children are placed at home with parents or with kinship caregivers, relational skill building services that include financial assistance for child care, respite and transportation services. EPIC participants receive substance abuse and behavioral health treatment services through local providers including from two partner agencies: Integrated Services for Behavioral Health and Ohio Guidestone.

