### Consent and withdrawal from study

Child welfare caseworkers obtain written informed consent and release of information from all parents at intake prior to study enrollment. Kinship caregivers consent for their own participation. Participation is voluntary and participants are free to withdraw from the study at any time without consequences to their child welfare cases.

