### Statistical plan

Baseline descriptive statistics including sociodemographic characteristics, addiction severity and child welfare allegations will be provided for EPIC participants and comparison groups. For continues variables, means and SDs will be provided and for categorical variables, counts and percentages are provided.

Due to the likelihood of censored measures when families are still involved in the child welfare system, survival analysis will be utilized to assess program effects on length of stay in out of home care. Logistic regressions will be used to estimate the relationship between activities and family was reunification, subsequent child maltreatment investigations, and subsequent child maltreatment substantiations. A series of linear regressions will be used to estimate the relationship between our outcome measures and various independent variables (e.g., age, biological sex). Additionally, a paired samples t-test will be conducted to examine the changes in mean scores in child, parent and caregiver well-being outcomes (e.g. ASI or CBCL) between baseline and 6-months follow-up.

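### The four stated powers (1.00, 0.81, 0.88, 0.99) are presented as powers for one small effect of 0.2, but no single reading tried gives all four, and none is for a 250 v 250 comparison

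*Protocol article*

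**What the plan says.** The Power analysis section uses one effect size, 0.2, described as small, for every method, with a Type I error of 0.05: "Assuming a small effect size of 0. 2, we will be able to reject the null hypothesis with probability (power) of 1.00". It reports "1.00 (survival analysis, *N* = 750"), "0.81 (logistic regression, *N* = 750"), "0.88 (paird t-tests; *N* = 250") and "0.99 (linear regression, *N* = 250"). It names no effect metric, contrast or event share in the text, and refers to Additional file 1 for detail.

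Other sections fix what these analyses are for:

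- Evaluation design sets three groups of 250 (EPIC, Ohio START, treatment as usual) and asks what EPIC adds beyond each of the other two.
- Objectives 2.1 to 2.3 under Methods / design compare EPIC with substance-affected families who do not receive it, which also allows 250 v 500.
- Statistical plan assigns survival analysis to program effects on length of stay: "Due to the likelihood of censored measures when families are still involved in the child welfare system, survival analysis will be utilized". It describes the linear regressions as relating outcomes to variables such as age and sex.

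**The concern.** An effect of 0.2 means different things as a standardised mean difference, a correlation, Cohen's f or f², a log odds ratio or a log hazard ratio. One value labelled small across four methods tells the reader that every analysis has at least 81% power for the same modest effect. If the figures belong to different effects, some of them not small, that assurance is wrong as printed.

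The risk lies in interpretation. Length of stay and reunification are named objectives. A null result on either, read against stated powers of 1.00 and 0.81, could be taken as evidence that EPIC has no effect, when the group comparison may have had much less power.

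**Working it through.** **Inputs from the article:** effect 0.2; N = 750 (survival, logistic) and N = 250 (paired, linear); alpha 0.05; groups of 250, 250 and 250. **Assumptions:** two-sided tests; no allowance for matching or for clustering by county; event shares and base rates as shown.

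**1. Paired t-test (stated 0.88).** Noncentrality = d√n = 0.2 × √250 = 3.162 on 249 df. Power = 0.883, so this figure reproduces.

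**2. Linear regression, N = 250 (stated 0.99).** Noncentral F with noncentrality f²N.

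| Reading | f² | Noncentrality | Power |
|---|---|---|---|
| r = 0.2, one predictor | 0.04/0.96 = 0.0417 | 10.4 | 0.895 |
| f = 0.2, one predictor | 0.04 | 10 | 0.883 |
| f² = 0.02, one predictor | 0.02 | 5 | 0.605 |
| f² = 0.2, 1 to 10 predictors | 0.2 | 50 | 1.00 |
| f² = 0.2, 30 predictors | 0.2 | 50 | 0.989 |

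More predictors lower the power: r = 0.2 with five gives 0.69. Solving for power 0.99 with one predictor gives f² = 0.074. The value f² = 0.2 corresponds to R² = 0.2/1.2 = 0.17, and is 0.2/0.0417 = 4.8 times the f² of r = 0.2. A one-sided test at r = 0.2 gives 0.94, still short of 0.99.

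**3. Survival, group contrast (stated 1.00).** Schoenfeld: power = Φ(|log HR| × √(D·p(1−p)) − 1.96), with D events and p the share in one group. Every one of the 750 families is given the event, the most favourable case.

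- 250 v 500: 0.2 × √(750 × 2/9) = 2.582, power 0.73.
- 375 v 375: 0.2 × √(750 × 1/4) = 2.739, power 0.78 (one-sided 0.86).
- Power that rounds to 1.00 (0.995) at 250 v 500 needs HR = exp((1.96 + 2.576)/12.91) = 1.42, still with no censoring.

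**4. Logistic, N = 750 (stated 0.81).** Wald: log OR divided by √(1/(n₁p₁q₁) + 1/(n₀p₀q₀)).

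- Group contrast, log OR 0.2 (OR 1.22), base rates 0.2 to 0.7: 0.19 to 0.28 over the 250 v 500 and 375 v 375 splits.
- Group contrast, OR = exp(0.2π/√3) = 1.44, the equivalent of d = 0.2: 0.51 to 0.70 over the same splits. Example: base rate 0.5, 250 v 500, p₁ = 0.590, SE 0.157, ratio 0.363/0.157 = 2.32, power 0.64.
- Covariate per standard deviation, |b|√(N·p(1−p)): log OR 0.2 at event rate 0.5 gives 2.739, power 0.78. OR 0.8 at event rates 0.3 to 0.5 gives 0.80 to 0.86. So 0.81 is reachable here.

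**5. One reading for all four?**

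| Reading of 0.2 | Survival | Logistic | Paired | Linear |
|---|---|---|---|---|
| Stated | 1.00 | 0.81 | 0.88 | 0.99 |
| Group log ratio 0.2, 250 v 500, no censoring | 0.73 | 0.19–0.25 | 0.88 | not a group contrast |
| Group ratio 1.44, 250 v 500, no censoring | 0.997 | 0.51–0.64 | 0.88 | not a group contrast |
| Log ratio 0.2 per SD of a covariate; r = 0.2 | 0.9998 | 0.78 | 0.88 | 0.90 |

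No row matches the stated figures throughout.

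**6. The 250 v 250 comparisons, for which nothing is stated.**

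- Mean difference d = 0.2: noncentrality 0.2 × √125 = 2.236, power 0.61.
- Log HR 0.2: 0.61 with 500 events, 0.35 with 250.
- HR 1.44: 0.98 with 500 events, 0.82 with 250.
- OR 1.44: 0.40 to 0.52. OR 1.22: 0.15 to 0.20.
- HR detectable at 80%: exp(2.802/√(D/4)) = 1.28 with 500 events, 1.43 with 250.

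**The case against.** The strongest defence is that the inputs sit in Additional file 1, which is not shown. It may name a metric, a predictor type and an event rate for each calculation. Two of the disputed figures are reachable under some reading: a standardised covariate with log HR 0.2 gives 0.9998 with 750 events and 0.998 with 600, a three-group test at f = 0.2 gives 0.999, and 0.81 fits a standardised covariate in the logistic model. A reader might therefore infer that each figure is an arithmetic error. The document does not support that. What stands is narrower: the printed sentence claims one common small effect for all four, and that claim fails whatever the file contains. The covariate reading also does not serve the survival model, which the Statistical plan assigns to program effects.

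A reader might also infer that the between-group comparisons have power of only about 0.4 to 0.6. That is not fixed by the document. Across the readings above, 250 v 250 power runs from about 0.15 (OR 1.22) to 0.98 (HR 1.44, no censoring), and the range 0.4 to 0.6 comes from converting d to an odds ratio for one model but not for the other. The objectives also permit 250 v 500, where d = 0.2 gives 0.73. Nor can a group-contrast figure replace the 0.99, which belongs to a covariate regression.

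Attrition and removal are weaker points. Consent wording says "participants are free to withdraw from the study at any time", and some families are described "when children are placed at home with parents or with kinship caregivers, relational skill building services", so the number analysed may be below 250 or 750. No rate is given. As an assumption only, 20% loss would leave 200 pairs and power 0.80.

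**Conclusion.** The point holds as a misstatement in the Power analysis section. The four figures are not powers for one small effect of 0.2. The clearest case is linear regression, where 0.99 at N = 250 compares with 0.88 to 0.90 for f or r = 0.2 and one predictor; this needs no assumption about groups or events. Next is survival, where 1.00 compares with at most 0.73 to 0.78 for a group log hazard ratio of 0.2, before any of the censoring that the plan itself expects. The 0.81 is not shown to be wrong, but it does not describe the group contrast at OR 1.22 or 1.44. None of the four figures describes EPIC v Ohio START or EPIC v treatment as usual at 250 per group.

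These results assume two-sided 0.05 and ignore matching and county clustering. The between-group figures depend on the chosen metric and event share and should be quoted only with them.

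**What to change.** Replace the single sentence with one line per analysis stating:

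- the contrast (EPIC v Ohio START, EPIC v treatment as usual, or EPIC v both pooled) and n per group;
- the effect in its own metric;
- for survival and logistic models, the assumed event share or base rate.

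For linear regression, either state the f² and number of predictors used and delete the word small, or restate power as about 0.90 for r = 0.2 with one predictor. For survival, restate power for the group contrast under the expected censoring, for example as the hazard ratio detectable at 80% with 250 v 250: 1.28 if all 500 families have the event, 1.43 if half do. If the paired test is shown at a reduced number of completers, or survival at a reduced number of removed children, label the rates as assumptions.

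The cost is wording only. The stated figures become less favourable; no analysis changes and no extra enrolment is needed.

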**Methods:**

EPIC is a quasi-experimental study. Under the program**,** child welfare-involved adults who screen positive for substances are matched with a peer recovery supporter. Participants are also incentivized to participate in family treatment drug court, medications for opioid use disorders and home-based parenting supports. Participating adults (*N* = 250) are matched with comparison groups from counties participating in a separate intervention (Ohio START) and to those receiving treatment as usual, resulting in a final sample of 750 adults. Primary outcomes including addiction severity, child trauma symptoms, resilience, and attachment are assessed at baseline and at program completion. Additional outcomes include timely access to treatment services, length of placement in out-of-home care and recidivism into the child welfare system.

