**Fig. 1 Fig1:**
[figure not shown]
Enhancing Permanency in Children and Families (EPIC): Case Flow. Parents complete the UNCOPE assessment within 7 days of substantiated report of child abuse or neglect. Parents receive a drug screen if they self-identify on the UNCOPE or a caseworker suspects substance use. Parents who screen positive are eligible for EPIC and are 1) linked to a peer recovery supporter, 2) referred to family treatment drug court, with the option of medications for opioid use disorders, and 3) receive in-home parenting based on the Nurturing Parenting Program. Participants work with assigned caseworkers to determine the most appropriate combination of services

To incentivize participation in FTDC, parents receive a $200 gift card upon completing their substance abuse assessment and an additional $200 retails gift card for every 3 months they remain involved with the court. Parents may consent to one or all three components of EPIC based on the specific needs of each family, however all parents receive intensive case management services, including frequent home visits from caseworkers and peer recovery supporters. All procedures involving human participants were approved by The Ohio State University’s Institutional Review Board (#2018B0001).

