### Evaluation design

To evaluate EPIC, a quasi-experimental design will be employed through a two-stage sampling procedure. This design provides the ability to assess (1) the effects of EPIC on access to services for the families in the two intervention counties, and (2) the independent effects of additional services provided under EPIC that may be over and above interventions provided by Ohio START and treatment as usual (TAU). In the first stage, two comparison counties will be identified for each of the two intervention counties. One comparison county will be part of the Ohio START program while the second will be a county that has no major interventions to address substance use among child welfare families. Counties are matched based on child population size, rate of child protective services referrals, percent of naloxone administrations per adult population, percent white, percent poverty, child welfare tax levy, and to the extent possible, behavioral health service availability. During the second stage, EPIC families (*N* = 250) are matched with substance using families in Ohio START (*N =* 250) and those receiving treatment as usual (*N =* 250).

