#### Sample characteristics

To describe the sociodemographic characteristics of participants, all surveys include demographic information (e.g., biological sex, age, race/ethnicity, nativity). In addition, a clinical description of the sample will be provided using the 10-item Center for Epidemiological Studies-Depression (CES-D) scale for depressive symptoms [35], the Perceived Stress Scale (PSS) [36] and perceived availability of social support using the Interpersonal Support Evaluation List (ISEL) [37]. *Timely access to services* is measured using dates of substance abuse screenings, trauma assessments and treatment service provision recorded in the Needs Portal.

*Child safety and permanency* outcomes are operationalized as (1) the number of days in out-of-home care, (2) whether the family re-unifies in out of home care and (3) the number of new child welfare referrals occurring after the initial referral that led to program participation using administrative child welfare data from the statewide automated child welfare information system (SACWIS).

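### N = 750 and its power are stated for length of stay and reunification, but entry does not require a child in out-of-home care, so neither figure holds for these two outcomes unless every family has a placed child

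*Protocol article*

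**What the plan says.** **Entry.** Under Participant recruitment, eligibility and group assignment: "Parents who score a 3 or higher on the UNCOPE, are considered eligible for EPIC and receive a drug screen". The legend to Fig. 1 says "Parents who screen positive are eligible for EPIC". Neither sets a condition on where the child lives. The same recruitment section offers relational skill building "when children are placed at home with parents or with kinship caregivers".

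**Sample.** The abstract describes matching EPIC adults to two comparison groups, "resulting in a final sample of 750 adults". Under Evaluation design, the 250 EPIC families "are matched with substance using families in Ohio START" and with families under treatment as usual, 250 in each group. The matching variables listed there are county-level. Those used at family level are not given.

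**Outcomes and methods.** The permanency outcomes include "1) the number of days in out-of-home care, (2) whether the family re-unifies". The Statistical plan says "survival analysis will be utilized to assess program effects on length of stay in out of home care", which is the only use named for that method. Logistic regression serves three outcomes: reunification, later investigations and later substantiations.

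**Power.** With effect size 0.2 and type I error 0.05, the Power analysis section gives "1.00 (survival analysis, *N* = 750), 0.81 (logistic regression, *N* = 750". It states power by method, not by outcome, and refers to an additional file that is not shown here.

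**The concern.** A family whose child is never placed has no stay to end and no reunification to reach. The entry rule admits such families, and the text on relational skill building suggests that some are expected. The N printed for the survival analysis is nevertheless the whole matched sample, and length of stay is the only outcome that method serves. For reunification, the only N and power in the article are likewise those of the full sample.

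Two things are at stake. First, a reader relies on a power for reunification and length of stay that the design delivers only if every enrolled family has a placed child. Second, the article does not say how never-placed families would be handled, and the choice matters because the comparison groups come from different counties. Coding these families as not reunified would count against a program that keeps children at home. Coding them as 0 days would let differences between counties in removal practice drive the comparison. Dropping them leaves an N below 750.

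**Working it through.** **Inputs from the article:** N = 750 (3 × 250); effect size 0.2, metric not stated; alpha 0.05, sidedness not stated; power 1.00 (survival) and 0.81 (logistic). **Assumption:** the share *s* of families with a placed child, which the article does not give.

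**Step 1: reproduce the stated figures.**
- Calibration: a two-sided paired t-test with d = 0.2 and N = 250 gives 0.883, matching the stated 0.88.
- Survival: reading 0.2 as w, with noncentrality N × 0.2² = 750 × 0.04 = 30, gives 1.000 (1 df) or 0.999 (2 df). This matches 1.00. Reading it as a hazard ratio of 0.8 with all 750 as events and equal groups gives Φ(√(750/4) × 0.223 − 1.960) = 0.863, which does not match.
- Logistic: a standardised covariate with odds ratio 1.2, event rate 0.5 and a one-sided test gives Φ(√(750 × 0.25) × 0.182 − 1.645) = 0.803. Odds ratio exp(0.2), event rate 0.3, one-sided, gives 0.807. Both are close to 0.81.

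These matches are possible but not unique, because the article omits the metric, the sidedness and the event rate. Each of them treats all 750 families as informative.

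**Step 2: reduce N to the placed families.**
- Reunification, simple scaling of the stated power: 0.81 at N = 750 corresponds to 1.960 + 0.878 = 2.838, so power = Φ(2.838 × √s − 1.960).
 - s = 0.7: Φ(2.374 − 1.960) = 0.66
 - s = 0.5: Φ(2.007 − 1.960) = 0.52
 - s = 0.3: Φ(1.554 − 1.960) = 0.34
- Reunification, second route: the odds-ratio 1.2 formula above at the reduced N.
- Length of stay: noncentral chi-square with noncentrality 0.04 × N.

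| Assumed placed share | N | Reunification, scaled | Reunification, OR 1.2 | Length of stay, w = 0.2 (1 df / 2 df) | Length of stay, HR 0.8 |
|---|---|---|---|---|---|
| 100% | 750 | 0.81 | 0.80 | 1.000 / 0.999 | 0.863 |
| 80% | 600 | 0.72 | 0.72 | 0.998 / 0.995 | 0.780 |
| 70% | 525 | 0.66 | 0.67 | 0.996 / 0.989 | 0.725 |
| 50% | 375 | 0.52 | 0.55 | 0.97 / 0.94 | 0.579 |
| 30% | 225 | 0.34 | 0.39 | 0.85 / 0.77 | 0.387 |

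The last column is shown for range only. It does not reproduce the stated 1.00, and it counts every placed child as having the event.

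**The case against.** The strongest reply is that nothing in the article puts never-placed families into these analyses. An analysis of length of stay ordinarily starts at placement, power is given by method, and denominators for each outcome may be in the additional file or the full plan. This stands as far as it goes. A reader might infer that the plan will code never-placed families as 0 days or as not reunified, but no section says so, and those harms are conditional. It does not rescue the printed figures: if the analyses are restricted to placed families, 750 is not their N unless every family has a placed child.

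Other parts of the reply also stand:
- A reader might take the logistic N = 750 as wrong throughout. It is right for later investigations and substantiations, for which every family is at risk. It fails only for reunification.
- The wording on relational skill building governs when one service is delivered. It could also cover children returned home, and kinship care may itself be out-of-home care. It shows that children at home are foreseen, not how many were never placed.
- A child at home at entry may be placed later, so the point concerns families never placed.
- A reader might infer that matching ignores placement. Family-level matching variables are not listed, so this cannot be said.
- A reader might estimate the placed share from the Pickaway figures (46 foster placements in 2018, 67% of families with substance problems). Those figures mix children with families, leave out kinship care and Fairfield County, and have no usable denominator.
- Zero is a possible value of a count of days in care, and keeping every family avoids conditioning on later removal. But that is a different quantity from length of stay analysed by survival methods, and it depends on removal practice.

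**Conclusion.** The point holds for the stated N and power of length of stay and reunification. Entry is by substance screen, children at home are foreseen, and the full 750 is assigned to a survival analysis that serves length of stay alone and to a logistic power figure that is the only one offered for reunification.

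The size depends on a placed share that the article does not report. Reunification loses materially even at a high share: about 0.72 at 80%, and 0.52–0.55 at 50%. Length of stay is less sensitive under the reading that reproduces 1.00: about 0.94–0.97 at 50% and 0.77–0.85 at 30%. The scaling assumes that the effect size and event rate are unchanged among placed families, and that these are spread evenly over the three groups.

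Severity is moderate. The abstract names addiction severity, child trauma symptoms, resilience and attachment as primary, and puts length of placement among additional outcomes. Reunification is not in the primary list either. The documents do not support the stronger reading that the permanency results will be biased by miscoded families. They support only that the handling is not stated and that the printed N and power do not fit.

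**What to change.** 1. Define the analysis set for length of stay and reunification as families with a child in out-of-home care, by one SACWIS rule and one index window applied identically in EPIC, Ohio START and treatment as usual. State whether kinship placement counts.
2. Match on placement status, or within it, so that restricting to this set keeps the matched comparison.
3. Report removals after the index window as a separate outcome among families whose children were at home.
4. Restate N and power for length of stay and reunification from the expected placed share, giving the effect-size metric, the sidedness and the expected numbers of exits from care and reunifications. Keep N = 750 for later investigations and substantiations.

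The cost is protocol wording and one matching variable from SACWIS data already obtained quarterly, with no extra families or surveys. The downside is a lower stated N and power for these two outcomes, and stays that begin after the index window are reported separately from the main length-of-stay comparison.
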